# Energy management education for persons living with long COVID-related fatigue (EMERGE): protocol of a two-parallel arms target trial emulation study in a multicentre outpatient intervention setting with an online control group register

**DOI:** 10.1136/bmjopen-2024-098574

**Published:** 2025-02-07

**Keywords:** Fatigue, REHABILITATION MEDICINE, Post-Acute COVID-19 Syndrome, Self-Management

## Abstract

**ABSTRACT:**

**Introduction:**

Energy management education (EME) is a manualised, evidence-based self-management education programme developed and delivered by occupational therapists for persons living with chronic disease-related fatigue. Studies have shown that EME can positively affect self-efficacy, fatigue impact and quality of life in persons with chronic conditions, while data on persons with long COVID are lacking.

The primary aim is to evaluate if adding EME to the standard care improves outcomes in persons with long COVID-related fatigue. The secondary aim is to explore the energy management behavioural strategies applied in daily routines and investigate the influencing factors of implementing behavioural changes. The third aim is to perform a cost-effectiveness analysis of EME.

**Methods and analysis:**

Using observational data, we will emulate a prospective two-parallel arms target trial to assess whether adding EME to the standard care is associated with improved outcomes in patients with long COVID-related fatigue. The estimated sample size to detect a post-intervention difference of 1.5 points in self-efficacy to implement energy conservation strategies with 90% power (0.05 alpha) is 122 people (1:1 ratio).

Persons with long COVID-related fatigue who follow EME as part of their standard care will be recruited and included in the experimental group (EG), while potential participants for the control group (CG) will be recruited from a register and prospectively matched to a participant in the EG by applying the propensity score technique. The ‘standard of care’ of the CG will include any intervention, except occupational therapy-based EME in peer groups. The causal contrast of interest will be the per-protocol effect. Four self-reported questionnaires (fatigue impact, self-efficacy in performing energy management strategies, competency in performing daily activities, health-related quality of life) will be administered at baseline (T0; week 0), after lesson 7 (T1; week 6), post-intervention (T2; week 14) and follow-up (T3, week 24). Our main assessment will be at T2. Disease-related and productivity cost data will be collected, and a cost-effectiveness profile of the EME intervention will be compared with standard care.

**Ethics and dissemination:**

Ethical approval has been obtained from the competent Swiss ethics commission.

Findings will be reported (1) to the study participants; (2) to patient organisations and hospitals supporting EMERGE; (3) to funding bodies; (4) to the national and international occupational therapy community and healthcare policy; (5) will be presented at local, national, and international conferences and (6) will be disseminated by peer-review publications.

STRENGTHS AND LIMITATIONS OF THIS STUDYThis study will use a target trial emulation approach, which presents an alternative to a randomised controlled trial design when it is unethical or impractical.This study will deliver data on the effectiveness of an intervention recommended by guidelines and its cost-effectiveness.The problem of confounders in observational studies will be counteracted by using a propensity score matching technique, but not completely solved.

## Introduction

 Post-COVID-19 condition, also known as long COVID, occurs in individuals with a history of probable or confirmed SARS-CoV-2 infection, usually 3 months from the onset of COVID-19, with symptoms that last for at least 2 months, and cannot be explained by an alternative diagnosis.^1^ Prevalence estimates a range from 2.3% to 53% in adults.^2^ Long COVID may be more common in persons with a more severe acute illness or preexisting conditions.^3^

According to systematic reviews, fatigue, post-exertional malaise and dyspnoea are the most reported symptoms.^4 5^ Fatigue is experienced mainly as severe, impacting cognition, extended activities of daily living and social activities,^6^ which causes significant distress and disability to individuals, preventing their return to previous life routines, work and social life.^7^ Research on primarily mild-to-moderate and non-hospitalised SARS-CoV-2 cases reported that approximately 12%–23% of affected persons remained absent from work (or had long absence periods) at 3–7 months after acute disease.^2^

Currently, national and international guidelines, still mainly based on expert opinion, indicate a multidisciplinary approach for managing long COVID-related fatigue. This approach includes in addition to occupational therapy (OT), physiotherapy or psychological interventions, self-management education, peer support and symptom management strategies.^8^,^10^ The body of evidence supporting rehabilitation programmes for people with long COVID is gradually increasing, though it remains limited. According to a recent systematic review,^11^ which included studies up to May 2022, the evidence supporting physical training and breathing exercises to reduce fatigue and improve physical capacity and quality of life is limited. Another systematic review of registered interventional clinical trials for post-COVID syndrome, with a search date of September 2022, found that 168 out of 388 trials focused on physical rehabilitation, while only four trials focused on educational interventions.^12^ The most recent review and meta-analysis,^13^ which searched for randomised controlled trials (RCTs) until December 2023, included 24 trials with totally 3695 individuals. It identified “moderate certainty evidence that an online CBT programme probably improves fatigue and concentration, and a combined programme of physical and mental health rehabilitation probably increases the proportion of patients who experience recovery or important improvements” (p.9). Moderate certainty evidence was found for intermittent aerobic compared with continuous exercise, probably improving physical function. Despite OT, and particularly the use of energy management strategies, being one of the recommended interventions for persons with long COVID-related fatigue, data are missing on its effectiveness in managing the impact of fatigue on daily life and their costs.

Since 2021, many healthcare providers in Switzerland have started providing interprofessional in- and outpatient rehabilitation programmes for persons with long COVID. In a citizen science project in Switzerland in 2021, persons with long COVID discussed and identified the needs of affected persons. From a patient-centred perspective, rehabilitation and chronic care management, availability of interfaces for treatment continuity, availability of specific healthcare structures and knowledge among professionals were being identified as priorities for a research agenda and allocation of funding resources.^14^ Switzerland has not implemented a long COVID register yet.

Self-management education is the primary OT approach for persons with chronic fatigue syndrome^15^ and populations with chronic disease-related fatigue. Self-management refers to an individual’s ability to manage the symptoms, treatment, physical and psychosocial consequences and lifestyle changes inherent in living with a chronic condition.^16^

In 2017, group-based energy management education (EME)^17^ was developed for persons with multiple sclerosis-related fatigue. A detailed treatment manual and workbook for participants were written based on evidence-based intervention protocols for energy conservation^18^ and cognitive–behavioural therapy approaches,^19^ enriched with new elements from behavioural theories,^20 21^ principles for adult education and the inclusion of opinions from users and OT experts.

Since the beginning of the COVID-19 pandemic, occupational therapists (OTs) played a role in treating people with acute and post-acute COVID-19 and post-COVID-19 conditions in different settings (acute care, inpatient rehabilitation and outpatient reintegration). High-impact symptoms such as fatigue or post-exertional malaise affect the performance in daily activities, social participation and well-being. Some EME-trained OTs have started to include persons with post-COVID-19 condition-related fatigue in their EME groups or used the EME materials as part of individual therapy. In May 2021, nine OTs reported that the EME protocol was feasible and appropriate, although some optimisations for persons with long COVID-related fatigue were necessary.^22^ Since March 2021, the Clinic for Neurorehabilitation Basel (REHAB) has provided interprofessional consultation and day-hospital treatment programmes for persons with long COVID. EME is the standard OT intervention for persons with fatigue. In this clinical context, we performed a feasibility study in 2022 using a mixed-method design^23 24^ to improve the treatment materials and to prepare this study with promising results.

The purpose of this project is threefold. The primary aim is to evaluate if adding EME to the standard care improves outcomes for persons with long COVID-related fatigue. The secondary aim is to explore the energy management behavioural strategies applied in daily routines after participating in EME and investigate the influencing factors of implementing behavioural changes. The third aim is to perform a cost-effectiveness analysis of EME.

## Methods and analysis

### Project status

The recruitment at the three intervention group sites and for the control group (CG) register started in July 2024. The time between registration in the study and matching for the CG depends on the recruitment rate of the EME participants. The first matching of 15 participants of the experimental group with 15 participants out of the CG register was performed in December 2024. Study participation lasts for each study participant approximately 24 weeks; therefore, data collection was not finished with any participant before submission of this article. The recruitment will be finished during late summer/early autumn 2025, and data collection will be finished at approximately the end of 2025.

Data analysis will begin at the end of 2025 after the last participant has completed T3. The total duration of the research project is 42 months.

### Study design

The gold standard for investigating the efficacy of a treatment is an RCT, which guarantees high internal validity by minimising clinician and patient biases. In contrast, pragmatic trials prioritise external validity by studying interventions in the context of broad-based and normal clinical practice conditions.^25^ In rehabilitation research, pragmatic or real-world trials are increasingly being conducted.^26^ They aim to identify the most effective intervention for a patient-centred primary endpoint.^27^

Considering the above elements of the current context, we will emulate a prospective interventional study that draws causal inferences on the effectiveness of adding EME to standard care using a target trial emulation approach.^28 29^ Ethical approval has been obtained from the competent Swiss ethics commission (2024–00938; Rif. CE 4596).

### Interventions

*Standard care:* any interventions tailored to the specific needs and goals that aim to support individuals with long COVID on their way back to normality, such as breathing exercises, individual OT, relaxation techniques, mindfulness, cognitive–behavioural therapy, physical exercise training and consultations by different health professionals (eg, physicians, cardiologists, pulmonologists, psychologists, dietitians and social workers). All participants will follow the standard care personalised to their needs and preferences. The CG will receive the standard care only.

*Energy management education (EME), revised outpatient version 2023:* this updated version integrates the findings of the feasibility study performed in 2022.^23 24^ EME aims to increase self-management skills for managing the available amount of energy and achieving a satisfactory and meaningful daily routine despite fatigue. During EME, participants learn about the factors influencing their energy level and experiment with skills to manage their energy using behavioural strategies (eg, pace, plan and prioritise activities and optimise communication, environment and ergonomic behaviour). Subsequently, they identify and implement tailored behavioural modifications. To support the reflection on and use of energy-managing strategies and new behaviours, the leading OTs use behavioural change techniques.^21^ The outpatient EME protocol consists of seven group sessions (90 min) once a week plus an eighth session approximately 8 weeks after the seventh one. The first, seventh and eighth sessions can be done in individual sessions (45 min) alternatively. Sessions are led by EME-trained OTs. The experimental group will receive personalised standard care plus EME. The overview of the topics and further details are presented in table 1.

**Table 1 T1:** Intervention: energy management education, revised outpatient version 2023

Structure	Delivery modality/duration		Topics	Applied behavioural change techniques
Lesson 1	Individual or group face-to-face/45 min or 90 min.	Self-training tasks	Energy account	Shaping knowledge, experience exchange and social support, feedback and monitoring, compared behaviour and outcomes, goals and action planning, antecedents, self-belief
Lesson2–6	Group face-to-face (3–7 participants)/90 min /once per week		Break management.Occupational balance.Successful communication.Simplifying.Think organised.	
Lesson 7	Individual or group face-to-face/ 45 or 90 min.		Apply in daily life	
Lesson 8 (Booster)	Individual or group, approx. 8 weeks after lesson 7		Review and reinforce	

At the University Hospital Bern (INSEL) and Clinic for Neurorehabilitation Basel (REHAB), the intervention starts with an individual lesson (45 min), whereas at University Hospital Zürich (USZ), the first lesson is already delivered in groups (90 min). With a frequency of one lesson per week, lessons 2–7 are provided (duration 90 min, appr. five participants). EME finishes with a group lesson, approximately 8 weeks after lesson 7. REHAB provides lessons 7 and 8 as individual lessons of 45 min. The EME-leading OTs use the treatment manual, which describes in detail the tasks of each lesson. All EME participants receive the workbook, which contains relevant information on the topics covered in each session, including worksheets and space for personal notes plus self-training tasks.

### Setting and recruiting

*Experimental group (EME, outpatient version 2023, plus standard care):* persons with long COVID-related fatigue following EME (revised edition 2023) in an outpatient setting at USZ, INSEL or REHAB, as part of their clinical routine and standard care, will be informed about this ongoing research and will be kindly asked if they are willing to participate in this project. If individuals agree, have signed the consent form and meet the inclusion/exclusion criteria checked by the study therapist on site, they will be included in the experimental group (EG). In these three public institutions, a group of trained OTs leads continuously EME groups and has received up-to-date training for the EME version 2023 in Spring 2024.

*CG (standard care*): a register of potential CG participants will be created through a contact with the Altea Network for Long COVID Association (ALTEA) and the patient organisation Long Covid Switzerland (LCS), both of which are partners in the study project and have been involved since the design phase. Using the contacts of ALTEA, LCS and specialised healthcare providers, information about the study will be disseminated, allowing interested persons to register themselves through a public link or QR code and to participate in a first online survey. Registration for the study has been open since 15 July 2024 and will remain open until summer 2025. Thereafter, based on the sociodemographic characteristics and clinical history of COVID-19, the CG participants will be selected from the register by their propensity score (PS) and matched with EG participants. Subsequently, the selected persons from the CG will be screened for eligibility, asked for their informed consent and included in the study.

### Eligibility criteria

The target study population consists of individuals aged 18 years or older, living in Switzerland, with a post-COVID-19 condition and a confirmed experience of fatigue. Eligible participants must not have major depression and/or significant cognitive impairments, must have sufficient ability to understand and speak one of the national languages and must provide signed informed consent. Persons are not eligible if they have previously participated in an EME group, have insufficient comprehension of one of the national languages or have a history of severe neurological diseases (eg, stroke, multiple sclerosis, Parkinson’s disease) or mental health disorders (eg, schizophrenia, major depression, or dementia).

### Objectives

The primary aim is to compare the effectiveness of the standard care for persons with long COVID-related fatigue plus participating in an EME group (revised edition 2023), with the standard care without EME at post-intervention (T2; week 14).

The secondary aim is to assess the energy management behavioural strategies applied in daily routines in persons living with long COVID, their feasibility and the factors influencing behavioural changes (T3, week 24).

The third aim is to evaluate the cost-effectiveness profile of the intervention by performing an economic evaluation alongside the trial.

### Outcomes

#### Primary outcomes

The impact of fatigue on physical, mental and social activities of daily routines will be measured with the Modified Fatigue Impact Scale.^30^ It contains 21 items, on a scale from 0 (never) to 4 (almost always), thus total ranging from 0 to 84.Self-efficacy in performing energy management strategies is the most proximal outcome of EME. Increased perceived self-efficacy in performing energy management behaviours and strategies correlates to the impact of fatigue in daily life and predicts behavioural changes after patient education. This will be measured using the ‘Self-Efficacy for Performing Energy Conservation Strategies Assessment’.^31^ This self-report questionnaire reports the mean scores of perceived confidence in performing 14 different energy management strategies (1=low confidence, 10=high confidence). It is a valid and reliable instrument with a minimal clinically important difference of 0.92 in people with chronic conditions and fatigue.^32^

#### Secondary outcomes

The Occupational Self-Assessment (OSA 2.2^33^; focuses on perceived competency to perform 21 daily tasks, which scores from 1 (I have many problems) to 4 (I do extremely well). The raw data are converted to interval levels (0–100). OSA has been validated in German and has shown the ability to detect changes in self-reported competence for daily activities over time.^34^Health-related quality of life will be measured by using the Short-Form 12 Item Health-Related Quality of Life Survey. This survey is a practical, reliable, valid and often used measure of physical and mental health. It assesses the same eight health domains as the SF-36,^35^ but with only one or two questions per domain: Physical Functioning, Role-Physical, Bodily Pain, General Health, Vitality, Social Functioning, Role-Emotional and Mental Health.^36^ Each health domain score contributes to the Physical Component Summary and Mental Component Summary scores.The Behavioural Changes in Energy Management Survey will be administered to describe the stable use of energy management strategies in daily life. This survey consists of eight questions and documents changes in using energy management strategies in daily routines, the effectiveness of stable strategy use (VAS 0–10), the simplicity of implementing them (VAS 0–10) and the actual stage of change. This survey has been used in two previous studies^23 37^ and was feasible (complete filled-out questionnaire response rate: 70%, average response duration: 10 min).

For the *cost-effectiveness* profile of the EME intervention assessed vs the standard care comparator, a self-reported questionnaire will be administered at several measure points to collect disease-related and productivity cost data allowing a more comprehensive assessment of the cost dimension. The dimensions for which data are collected include not only the ability to work and its remuneration and medical costs but also changes in costs, for example, mobility, leisure time and support at home.

### Patient and public involvement

With Altea Network for Long COVID Association (ALTEA) and the patient organisation Long Covid Switzerland (LCS) as project partners, the two relevant patient associations in Switzerland are part of this research project during all steps from the very beginning until the end. They participated during the protocol development like giving feedback about targeted research questions and outcome measures (eg, adequacy and burden), co-developed most patient information (informed consents, flyers, posts for social media, etc), are actively involved in the recruitment for the CG register and are giving feedback and meanings from the patient community about our study.

These two associations will be participating in the interpretation of the results of this study and their dissemination by co-authorship at scientific publications and congress participation and by having the lead in the dissemination to the patient community as to the public and politics.

Voluntary study participants’ feedback was and will be taken seriously and has resulted in minor changes. Study participants and participants in the CG register will be informed about the results of the study and their dissemination.

### Data collection

All questionnaires and surveys will be available in the three national languages (German, French and Italian) for both groups and at all time points online via Redcap (http://www.project-redcap.org/). If preferred, they will also be available on paper, either delivered personally by the local investigator or sent by post. Self-reported questionnaires documenting the outcomes of interest will be collected at different time points. In tables2  3, all procedures and data collection time points involving the CG and the EG are listed, respectively.

**Table 2 T2:** Register and control group: timeline of contacts and assessments

Timeline contacts	Register	Study period control group (CG)						
	Enrolment		T0		T1		T2	T3
Weeks	>14	-2	0	4	6	9	14	24
Information about register and study procedures	x							
Informed consent for register	x							
Sociodemographic characteristics	x							
Clinical history of (post-)COVID-19-condition	x						x	x
Matching		x						
Check study inclusion/exclusion criteria		x						
Informed consent for CG participation		x						
Outcomes								
MFIS			x		x		x	x
SEPECSA			x		x		x	x
OSA			x		x		x	x
SF-12			x		x		x	x
BCEM-S								x
Disease-related costs				x		x	x	x

BCEM-SBehavioural Changes in Energy Management SurveyMFISModified Fatigue Impact ScaleOSAOccupational Self-AssessmentSEPECSASelf-Efficacy for Performing Energy Conservation Strategies AssessmentSF-12Short-Form 12 items

**Table 3 T3:** Experimental group: timeline of contacts, assessments and energy management education intervention

Timeline contacts	Study period experimental group (eg,)							
	Enrolment		T0		T1		T2	T3
Weeks	>14	-2	0	4	6	9	14	24
Announced to EME at USZ, REHAB, INSEL		x						
Screening and inclusion into EME		x						
Written information about the study		x						
Check study inclusion/exclusion criteria			x					
Informed consent			x					
Sociodemographic characteristics			x					
Clinical history of (post-)COVID-19-condition			x				x	x
EME intervention (lessons 1–8)			L1-2-3-4-5-6-7-------8					
Outcomes								
MFIS			x		x		x	x
SEPECSA			x		x		x	x
OSA			x		x		x	x
SF-12			x		x		x	x
BCEM-S								x
Disease-related costs				x		x	x	x

BCEM-SBehavioural Changes in Energy Management SurveyEMEenergy management educationMFISModified Fatigue Impact ScaleOSAOccupational Self-AssessmentSEPECSASelf-Efficacy for Performing Energy Conservation Strategies AssessmentSF-12Short-Form 12 itemsUSZUniversity Hospital Zürich

Reasons for discontinuation are the following: (1) withdrawal of informed consent, (2) participants from the CG (without EME) starting in an OT-EME group during the data collection phase and (3) participants of the EG (with EME) missing more than three of the eight EME lessons. All data collected until withdrawal will be used in the analysis. If a participant decides to withdraw from the follow-up, the reasons for the withdrawal will be recorded for the subsequent analysis respectively the interpretation of the results. We will make all attempts to closely follow up participants and therefore minimise missingness throughout data collection. At each time point, participants of both groups will be invited to fill in the questionnaires via Redcap by presenting or e-mailing the correct web link and, if necessary, up to two reminders after 4–5 days each. No reaction will lead to a reminder for contacting the principal investigator, if they need any support to continue with the study, with a clear statement, that they are not obliged to answer this reminder or justify their drop-out if they do not want to.

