### Statistical methods and analysis

#### Sample size

The target study population are people with post-COVID-19 condition living in Switzerland. To calculate the sample size of this study, we used data from two previous studies. In the feasibility study with persons with long COVID-related fatigue, the mean difference of the primary outcome (self-efficacy in performing energy conservation strategies) at T2 (post-intervention) was 1.9 (95% CI: 2.89 to 0.90).^23^ We hypothesised, therefore, a difference of 1.5 points at T2 and conservative assumption of a SD of 2.2 points.^38^ Including a follow-up rate of 24% at T2, the estimated sample size to detect a difference of 1.5 points with 90% power (0.05 alpha) is 122 persons. Therefore, we aim at a total of 122 persons included in the study (eg, 61 and CG: 61).

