#### Statistical analysis

We will emulate a prospective interventional study that makes causal inferences on the effectiveness of adding EME to the standard care using a target trial emulation approach (see table 4).^28 29^

**Table 4 T4:** Target trial protocol components

Protocol component	Emulated target trial
Eligibility criteria	Inclusion criteria: Living in Switzerland Age ≥18 years Diagnosed with post-COVID-19 condition Confirmed experience of living with fatigue (MFIS, cut-off >38)^47^ No major depression (Beck depression inventory (BDI)-FS cut-off <8)^48^ No major cognitive impairments (Mini-Mental State Examination (MMSE) cut-off of ≥26 for the experimental group and MMSE-telephone version for the control group (CG), cut-off≥21)^49 50^ Ability to understand and speak German, French or Italian and to fulfil the assessments Ability to give informed consent as documented by signature Exclusion criteria: Participation in an energy management education (EME) group or starting it during the study duration (only CG) History of severe neurological diseases (eg, stroke, MS and Morbus Parkinson’s disease) or mental health disorders (eg, schizophrenia, major depression, schizophrenia or dementia) Inability to follow the procedures of the study, for example, due to language problems, psychological disorders, dementia, etc.
Recruitment	Experimental group (eg,) participants at three study sites (INSEL, USZ, REHB) consecutive ongoing from mid-July 2024 up to the required number of 61 participants; maximum until end of 2025 A register for potential CG participants disseminated through the national patient organisations and specified healthcare providers
Follow-up	24 weeks after enrolment in the study

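### Controls face no ability-to-attend condition to mirror the experimental group's screening into EME, so the control arm can include people unable to attend it

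*Protocol article*

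**What the plan says.** **Experimental group (EG).** Under Setting and recruiting, the EG consists of people who already follow EME as routine outpatient care at one of three hospitals. Table 3 (Data collection) places "Screening and inclusion into EME" at week -2, before the study's own criteria are checked at T0. The Interventions section describes EME as "seven group sessions (90 min) once a week plus an eighth session approximately 8 weeks after the seventh one". EG members who miss more than three of the eight lessons are discontinued (Data collection).

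**Control group (CG).** Information is spread through patient organisations and specialised providers, "allowing interested persons to register themselves through a public link or QR code". Register members complete an online survey, are selected by propensity score, and are then screened and asked for consent. Cognition is checked with a telephone version of the test (Table 4), and questionnaires are answered online or on paper. Table 2 has no row corresponding to screening into EME.

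**Criteria and adjustment.** Table 4 requires residence in Switzerland and sets fatigue, depression and cognition limits. Its nearest item to an attendance condition is the exclusion for "Inability to follow the procedures of the study". The Statistical analysis section names sex, age and clinical history of fatigue as matching variables. It aims to add covariates such as fatigue intensity, fatigue impact, education and occupation status. The Selection bias section states that two-stage control recruitment with clear criteria yields effect estimates from a sample free of bias.

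**The concern.** A target trial has one eligible population, any member of which could be assigned to either strategy. Here one arm has passed a gate that the other has not. Everyone in the EG has been taken into, and is following, an on-site weekly group programme. A control need only complete consent, a telephone screen and questionnaires. Someone too limited to travel, or with no practical access to a site, can pass the control criteria but could not have entered the EG.

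Capacity to travel and to tolerate long sessions plausibly predicts how self-efficacy and fatigue impact develop over 14 weeks. If so, part of the T2 difference would reflect who was able to attend and not what EME did. The primary aim concerns the effect of adding EME, which has meaning only for people who could take it up.

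**Working it through.** **1. The two routes side by side**

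| Step | EG | CG |
|---|---|---|
| Source | Already following EME at three outpatient sites | Self-registration by link or QR code |
| Week -2 | Screened and taken into EME | Matching, eligibility check, consent |
| Cognitive screen | Standard version | Telephone version |
| Condition on attendance | Discontinued if more than three of eight lessons are missed | None |
| Residence | Must reach one of three hospitals | Anywhere in Switzerland |

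**2. Does any stated element close the gap?**
- *Eligibility.* The exclusion for inability to follow procedures works differently by arm, because control procedures involve no attendance. No other item in the Eligibility criteria section or Table 4 concerns ability or access to attend.
- *Matching.* Sex, age and clinical history of fatigue: capacity and access are not named. Table 2 lists the fatigue impact scale (MFIS) for controls first at T0, after matching.
- *Outcome model.* The named covariates capture part of severity, but not capacity or access.
- *Sensitivity analyses.* The E-value and simulated bias analyses gauge how strong an unmeasured confounder would have to be. They do not align the two populations.

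**3. The plan's own figure, to set the scale**

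Inputs from Sample size: "the estimated sample size to detect a difference of 1.5 points with 90% power (0.05 alpha) is 122 persons", with a "conservative assumption of a SD of 2.2 points", and "Including a follow-up rate of 24% at T2".
- Per arm (normal approximation): 2 × (1.960 + 1.282)² × 2.2² / 1.5² ≈ 45.2, so 46.
- With 24% read as loss to follow-up: 46 / 0.76 = 60.5, so 61 per arm and 122 in total. The stated figure is reproduced. It follows only if 24% means loss and not retention. This point does not dispute the sample size.
- Standard error of the T2 difference with 46 analysed per arm: 2.2 × √(2/46) = 0.459.

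**4. Size of the bias (assumed inputs)**

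Let f be the share of controls unable to attend and d the amount by which their 14-week change in self-efficacy falls short. The control mean is lowered by f × d, and the group difference is inflated by the same amount. The documents give neither f nor d. The range below is assumed, with no allowance for what matching and adjustment remove.

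| f | d | f × d | Share of 1.5-point target | Share of 0.92-point minimal important difference |
|---|---|---|---|---|
| 10% | 0.5 | 0.05 | 3% | 5% |
| 30% | 1.0 | 0.30 | 20% | 33% |

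If EME had no effect, a 0.30-point bias (0.30 / 0.459 = 0.65 standard errors) would raise the two-sided false-positive rate from 5% to about 10%. A 0.05-point bias would leave it at about 5%.

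**The case against.** **Possibility, not fact.** A reader might infer that the control arm does contain people who could never have received EME. The documents show only that nothing named excludes them. The content of the EME screening is not described, so ability and willingness are inferred from the EG already following EME. The clinical-history items in the register survey are not listed either. This stands, and the point is limited to what the control arm can include.

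**Severity.** A reader might infer that the comparison is simply confounded by severity. The documents do not support that. Both arms must exceed 38 on the MFIS and meet depression and cognition limits, clinical history enters the matching, and fatigue intensity and impact are intended covariates. What remains is functional capacity and access.

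**Direction.** A reader might infer that the EG is also the more motivated arm. Controls, however, are volunteers who seek out the study and complete a survey, as the Volunteer bias section acknowledges. For readiness the sign is unknown.

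**Overlap.** Each EG member is matched to a control, so the contrast describes people like those in the EG. Not every register member needs to be a candidate for EME, and inability to attend biases the result only if it is prognostic after matching and adjustment. This stands for distance alone, which need not be prognostic. It is less convincing for functional capacity.

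**Language.** A reader might infer that French- or Italian-speaking controls have no route to EME. The article never states the languages in which the sites deliver it, so this cannot be claimed. The plan also foresees controls starting an EME group, so some do have access.

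**Demands of EME.** Lessons 1, 7 and 8 may be individual sessions of 45 minutes, and up to three lessons may be missed. This softens the requirement, but lessons 2 to 6 remain weekly 90-minute face-to-face groups.

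**Already conceded in part.** The article admits residual confounding and volunteer bias. That lowers the weight of the point without addressing attendance.

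**Conclusion.** The asymmetry is in the text. EG entry depends on having been taken into on-site EME, CG entry has no corresponding condition, and no named criterion, matching variable or covariate covers capacity or access to attend. Residual bias therefore remains possible, plausibly in favour of EME as regards capacity and of uncertain direction as regards readiness.

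Its size cannot be derived from the documents. The 0.05–0.30 points are an illustration on assumed inputs, and even the upper end is below one standard error (0.459). This is a moderate weakness that can be corrected and does not invalidate the study. The one statement that should not stand as written is the Selection bias section's claim of a sample free of bias.

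**What to change.** 1. **Ask before matching.** Add to the register survey, or to the week -2 contact provided it is asked before matching is run, whether the person would be able to attend weekly on-site outpatient group sessions as EME requires. Match only those answering yes in the remaining batches. The article reports 15 of 61 pairs matched by December 2024, so this can still apply to up to 61 − 15 = 46 pairs.
2. **Record willingness, but do not exclude on it.** Keep willingness to join an EME group as a baseline variable for a sensitivity analysis. Restricting controls to those who would join now could select the people most likely to start EME, which is a reason for discontinuation in the CG.
3. **Controls already enrolled.** Ask them the attendance question and report the primary model with and without those answering no, as a sensitivity analysis only. Their answers come after baseline, and excluding on them in the main analysis could itself introduce selection.
4. **Wording.** Qualify the Selection bias statement to say that eligibility is aligned on the listed criteria, and that capacity and access to attend were not assessed in controls matched before the change.
5. **Language.** Do not add exact matching on language unless the sites' EME delivery languages are confirmed to differ from those of the controls.

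Cost: one or two questions in existing contacts, a short re-contact of people already in the register, a somewhat smaller pool, and possibly less close matches on the other variables.
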